##### Five facet mindfulness questionnaire (FFMQ)

Level of mindfulness is measured with the FFMQ, which consists of 29 items evaluating aspects of observing, describing, acting with awareness, non-judging of inner experience, and non-reactivity to inner experience [39]. The FFMQ is answered by the adolescents pre- and post-treatment. The construct validity of the scale is supported [39].

#### Secondary outcomes

##### Strength and difficulties questionnaire (SDQ)

Comorbid symptoms are assessed with the SDQ [40], a brief screening questionnaire with 25 items measuring symptoms of emotional and conduct problems, hyperactivity/inattention and peer problems, as well as prosocial behaviour. Moreover, the SDQ consists of an impact supplement targeting level of distress and social impairment. The Swedish version of the SDQ has shown adequate validity and is considered a useful tool for mental health screening in children and adolescents [41]. The SDQ is answered by both adolescents and their parents at pre- and post-treatment.

##### The hospital anxiety and depression (HAD) scale

As the SDQ, the HAD is used to assess comorbid symptoms [42]. The HAD contains 14 items that screen for symptoms of anxiety (seven items) and depression (seven items). This questionnaire is answered by the adolescents at pre- and post-treatment. The scale has been validated and has shown good psychometric properties in a sample of adolescents [43].

##### Pressure activation stress (PAS) scale

Perceived stress is measured with the PAS questionnaire [44]. It consists of 11 items that measure two dimensions of stress: feelings of pressure (e.g., from school demands) and activation (e.g., difficult to relax). The PAS is answered by the adolescents at pre- and post-treatment, as well as half-way through the SSTG. The scale display a promising face validity and good internal consistency [44].

##### Karolinska sleep questionnaire (KSQ)

The KSQ is a self-rating questionnaire measuring sleep problems [45]. In this study we use the seven items corresponding to the subscales “Difficulties falling asleep” and “Difficulties waking up”. The KSQ has shown adequate psychometric properties and is considered a useful tool to assess sleep problems [46].

##### Other measurements

Before and after treatment, parents are asked to report the adolescents’ current medication and dose of medication. During the treatment, the group leaders registered attendance and completed home assignments. During the final session, the adolescents completed an evaluation form specifically constructed for this study to assess the acceptability of the treatment. The evaluation form includes questions on how the participants perceived and responded to the treatment, the content and length of the treatment and if they would recommend the treatment to their peers.

### Statistical methods

#### Statistical analysis plan

The treatments were finalised during 2018 while post-treatment ratings are currently being collected. Analysis of the data will start in the summer of 2019. The statistical analysis will be conducted on all participants who completed the pre- treatment (baseline) questionnaires (*n* = 159 adolescents and *n* = 162 parents). Missing post-baseline data for any of the participants because of the absence of any session or dropout will be handled by multiple imputations using last mean carried forward (LMCF) [47]. A sensitivity analysis will be performed for those who completed the treatments (e.g., attended at least two thirds of the sessions) without using LMCF. Primary and secondary outcome variables will be analysed with repeated measurements in general linear models using the baseline value for respective outcome as a covariate. The primary analysis will be aimed at investigating differences between the two treatment groups in reduction in ADHD symptoms and functional impairment, and increase in mindfulness and quality of life, directly and 6 months post-treatment. Secondary analyses will be aimed at investigating the group treatment effects on reported symptoms of comorbid psychopathology and health-related status. Moreover, the two treatment groups will be compared for treatment acceptability. As separate analyses, we intend to explore any difference in outcome measures based on subgroups of clinical relevance (e.g., subtype of ADHD and symptoms of other psychopathology). We also plan to validate and investigate the psychometric properties of the newly developed questionnaire, IAS, which was constructed to assess the impact of ADHD symptoms on the adolescents’ wellbeing during the treatment intervention. Guidelines for the specific rating scale will be used in the choice of imputation of missing data within the scales. If no guidelines are available, an imputation of the mean of the subscale for that specific participant will be used when less than 20% of the items are missing.

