### Participants and procedures

Recruitment, treatment and data collection are conducted in seven cities in Sweden (Gävle, Falun, Karlstad, Uppsala, Uddevalla, Västerås and Växjö Additional file 1), beginning in 2015, with the last post-treatment measurement expected to be finalised in the spring of 2019. Adolescents (15–18 years of age) from the local child and adolescent psychiatric (CAP) outpatient units with a known diagnosis of ADHD have been informed about the study through flyers in waiting rooms, verbally by the clinical staff, or both. For those who have shown interest, more information has been provided at an extra meeting and the staff have evaluated the patients’ eligibility for the study (see below). Before final inclusion, participants and their parents provided written informed consent. Study participation is voluntary and can be interrupted by the participant at any time. Eligible patients have then been randomised to one of the two treatment conditions. Adolescent self-reports and parental ratings have been collected 2 weeks before the start of the treatment, during the treatment, and are continuously collected 2 weeks and 6 months after conclusion of the treatment. Pre- and post-treatment instruments are administered using an online platform to which only the research group has access and coded data is stored in a secure server. The participating parents are continuously reminded by the research team to complete the questionnaires. When both the adolescent and their parent have completed the last measurement, they will receive two cinema tickets. Initially, the plan was to continue the recruitment until at least 100 patients had completed treatment. In total, 184 patients have been randomised. Of these, 159 adolescents and 162 parents have completed baseline assessments and the last post-treatment evaluations are now continuously being collected (Fig. 1). Those who were randomised but never underwent a baseline assessment were considered external dropouts. Those who completed the baseline assessment, but did not complete the treatment, will be considered internal dropouts.

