### Outcome measures

#### Primary outcomes

##### Adult ADHD self-report scale for adolescents (ASRS-A)

ADHD symptoms are assessed using parental and self-ratings on the ASRS-A [33, 34] at pre- (baseline measurement) and post-treatment. Self-ratings were also conducted half-way through the SSTG. The ASRS-A is a modified version of the adult ADHD self-report scale. The instrument has shown promising psychometric properties in clinical populations [34]. The questionnaire contains 18 items corresponding to the diagnostic criteria of ADHD in accordance with the diagnostic and statistical manual of mental disorders, fourth edition (DSM-IV).

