##### Impact of ADHD symptoms (IAS)

A six-item questionnaire was constructed for this study to repeatedly assess the impact of ADHD symptoms on the adolescents’ wellbeing. The questionnaire is completed by the adolescents both at pre- and post-treatment but also after each of the sessions. The adolescent responds to the extent their wellbeing has been affected by behaviours and symptoms (e.g., difficulties in regulating emotions and starting/completing assignments on time) related to ADHD during the past week. Each item is answered on a scale from 0 (“Not at all”) to 10 (“Very much”), with higher scores indicating greater impact of the ADHD symptoms on wellbeing. The scale will be validated within the study.

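### Last mean carried forward can fill the two arms from different time points, so several self-rated outcomes may carry a biased arm difference that the stated sensitivity analysis cannot reveal

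*Protocol article*

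**What the plan says.** All references are to the protocol article.

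- **Imputation rule** (Statistical analysis plan). It covers "Missing post-baseline data for any of the participants because of the absence of any session or dropout", which "will be handled by multiple imputations using last mean carried forward (LMCF".
- **Model** (same section). Outcomes are analysed by "repeated measurements in general linear models using the baseline value for respective outcome as a covariate", directly after treatment and at 6 months.
- **Analysis set** (Participants and procedures). Of 184 randomised, "159 adolescents and 162 parents have completed baseline assessments".
- **Half-way ratings.** For ASRS-A: "Self-ratings were also conducted half-way through the SSTG". The CSDS section says the same of its self-ratings, and the PAS section also places a half-way rating in the SSTG. No half-way rating is described for the control arm.
- **Session ratings.** For IAS: "The questionnaire is completed by the adolescents both at pre- and post-treatment but also after each of the sessions". GQL follows the same pattern. The Trial arms section gives 14 sessions for SSTG and three for control.
- **Sensitivity analysis** (Statistical analysis plan). "A sensitivity analysis will be performed for those who completed the treatments (e.g., attended at least two thirds of the sessions) without using LMCF".

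**The concern.** A carried-forward mean treats a lost participant as unchanged since the last rating. If both arms were last rated at the same visit, the error from that assumption would at least arise at the same point in each. Here it need not. On self-rated ASRS-A and CSDS, both primary, an SSTG participant lost after half-way can be given a mid-course value, while a lost control participant can only be given a baseline value. On IAS and GQL, also primary, the last rating can come from late in a 14-session course in one arm and from no later than the third session in the other. Any change over time is then credited to different degrees in the two arms, and the gap enters the estimated treatment effect.

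ASRS-A and CSDS are also the scales on which the sample size rests. The one stated check on the rule changes the population and the imputation together. If its result differs from the main analysis, nobody can tell which change caused it.

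**Working it through.** **Figure in the plan.** The article gives no figure for missing data. Its sample size does reproduce: at effect size 0.57, two-sided 5% and 80% power, 2 × (1.96 + 0.84)² / 0.57² gives 49 per group, and the t-test gives 50, as stated. SD 12 and the 7-point ASRS-A change below come from that section.

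**Is there missingness?** 184 − 159 = 25 adolescents have no baseline, and the Discussion reports 32 who never started. So at least 32 − 25 = 7 of the 159 analysed (4.4%) had no treatment. Later dropouts add to this, but no rate is given. I assume 10 to 30%.

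**Bias formula.** Let p be the missing share, f the expected filled value and t the value that lost participants would truly have had (1 = SSTG, 0 = control):

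bias = p₁(f₁ − t₁) − p₀(f₀ − t₀)

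**No true effect, equal p.** Assume both arms fall 7 points from baseline B, 3.5 of them by half-way, and a share q of SSTG losses has a half-way rating. Then f₁ = B − 3.5q, f₀ = B, t₁ = t₀ = B − 7, so bias = p(7 − 3.5q) − 7p = −3.5pq. A negative value favours SSTG.

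| Missing per arm | q = 1 | q = 0.5 |
|---|---|---|
| 10% | −0.35 | −0.18 |
| 20% | −0.70 | −0.35 |
| 30% | −1.05 | −0.53 |

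Simulation with ANCOVA on baseline (about 80 per arm, SD 12, correlation 0.5, values missing completely at random) gives −0.36 to −1.02 over the same range with q = 1, and about half that with q = 0.5. ANCOVA on observed values shows no bias in this setting, as expected when loss is random.

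**The sign depends on the dropouts.** Now assume a true difference of 7, no control change, 3.5 points gained by half-way in SSTG, and q = 1:

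- Lost participants would have improved like the rest: bias = p × 3.5, against SSTG. Simulated: 0.33, 0.69 and 1.11 at 10, 20 and 30%.
- Lost participants return to baseline: bias = −p × 3.5, favouring SSTG. Simulated: −0.36, −0.62 and −1.10.
- As the previous case, but with no half-way rating available, 20% missing: 0.03, so the bias vanishes.

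Unequal loss matters too. In the no-effect setting with q = 1, 30% lost in SSTG and 10% in control gives 0.3 × 3.5 − 0.1 × 7 = +0.35, against SSTG.

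**Standard error.** In the no-effect setting at 25% missing:

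| Method | Reported SE | Actual SD of estimate | Type I error |
|---|---|---|---|
| Fixed fill | 1.53 | 1.69 | 11% |
| Carried mean as centre of multiple imputation, Rubin's rules | 1.98 | 1.60 | about 3% |
| ANCOVA on observed values | 1.91 | 1.94 | 5.2% |

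Over 10 to 30% missing, the fixed fill gives type I error of about 6 to 13%, part of it from the bias. The bias itself is much the same under both readings.

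**The case against.** The strongest defence is that the text says multiple imputations. A carried-forward mean can serve as the centre of an imputation distribution, with random draws and pooling. The number of imputations, the model and the pooling rule are details that an article may leave to a fuller plan. That stands. A reader might infer that one fixed value is put in each empty cell, so that standard errors are necessarily too small and the 5% level is lost. The article does not say so, and under the multiple imputation it names the standard error is too large.

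A reader might also quote type I errors of 10, 14 and 20% at 15, 25 and 35% missing. Those arise only when gaps are filled with the arm's own post-treatment mean, which carries nothing forward. A fixed fill from half-way (SSTG) and baseline (control), with no shared improvement, gives roughly 6 to 8% at 15 to 25% missing and about 9% at 35%.

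The scope is also limited. FFMQ, SDQ, HAD and the parent ratings are described with pre- and post-treatment points only, so unequal time points do not arise there. Nor do they arise for a missing 6-month value when the 2-week value is present. Control participants do have session ratings on IAS and GQL, so a fill from baseline is not the general case for those scales. The full bias needs every lost SSTG participant to have a half-way rating, and non-starters will not have one.

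Finally, a reader might fault the two-thirds attendance rule as unequal: 10 of 14 sessions against 2 of 3. It is the same proportion in both arms and is offered as an example, and any estimate of unequal pass rates needs an assumed attendance. The attrition analysis in the Discussion compares completers with non-completers, which is useful but does not test the imputation.

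What survives is the unequal carry-forward point, under either reading, and a sensitivity analysis that cannot isolate it.

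**Conclusion.** The point holds in a conditional form. If in-treatment ratings feed the rule, the arm difference on self-rated ASRS-A and CSDS, PAS, IAS and GQL can be biased. The inclusion of missed sessions among the causes of missing data suggests that they may, but the article does not say so outright. For ASRS-A the size is about 0.4 to 1.0 points favouring SSTG at 10 to 30% missing, or about half that when half of SSTG losses have a half-way rating. Against the planned 7-point difference, 0.35/7 = 5% and 1.05/7 = 15%. This rests on assumed missing rates, correlation, shared improvement and half-way change; other dropout behaviour changes or reverses the sign. I have put no size on IAS, GQL, CSDS or PAS.

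The standard error is not calibrated under either reading, but the documents do not settle its direction, so neither a general claim of false precision nor one of a lost 5% level is supported. This should be changed before analysis. It does not by itself undermine the trial.

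**What to change.** - **Primary analysis.** Replace the carried-forward mean with a likelihood-based mixed model for repeated measures on all observed ratings at the visits common to both arms (baseline, 2 weeks, 6 months). Alternatively, use multiple imputation by arm with a stated model and number of imputations, pooled by Rubin's rules.
- **In-treatment ratings.** State that half-way and session ratings are not carried forward as substitutes for post-treatment values.
- **Sensitivity analysis.** Keep the same population as the primary analysis and vary only the assumption about lost participants, for example by delta-adjusted imputation in each arm.
- **Completer analysis.** Keep it as supplementary.
- **If the present rule is kept.** Say whether it is a fixed fill or the centre of an imputation distribution, whose mean is carried, and from which visits.

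The cost is revised wording, modest programming and possibly wider confidence intervals. The article says that treatments have ended and that analysis has yet to start, so the change can be made before results are seen and reported as a deviation, as the Study design section already promises.

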**Methods:**

A sample of 184 adolescents (15–18 years of age) with a diagnosis of ADHD has been recruited from seven child and adolescent psychiatric outpatient units and randomised to either the SSTG or an active control group based on psychoeducation. Measures are conducted weekly during the treatment, as well as 2 weeks before treatment and 2 weeks and 6 months after treatment. The primary outcome measures are ADHD symptoms, functional impairment, quality of life and mindfulness. Secondary outcome measures are symptoms of comorbid psychopathology, perceived stress and sleep problems. This article describes the design, methods and analysis plan for evaluating the efficacy of the SSTG.

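### The repeated-measures general linear model is not tied to the two per-visit arm differences it is meant to deliver, and in its classical form the completer analysis run without LMCF would discard observed 2-week ratings

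*Protocol article*

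**What the plan says.** All the key statements are in the protocol article, Statistical methods, Statistical analysis plan.

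- **Model.** Primary and secondary outcomes are to be "analysed with repeated measurements in general linear models using the baseline value for respective outcome as a covariate".
- **Question.** "The primary analysis will be aimed at investigating differences between the two treatment groups" in the four primary domains, assessed "directly and 6 months post-treatment". The Methods paragraph of the abstract places the ratings outside the treatment period: "as well as 2 weeks before treatment and 2 weeks and 6 months after treatment".
- **Missing data, main analysis.** Everyone with baseline questionnaires is analysed (159 adolescents, 162 parents). Missing post-baseline values are imputed by last mean carried forward (LMCF).
- **Missing data, sensitivity analysis.** This is restricted to those who completed treatment, for example by attending two thirds of sessions, and is run "without using LMCF".

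The section does not say which model term or contrast gives the arm difference at each time. It also does not say what happens to a treatment completer who lacks one of the two later ratings.

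**The concern.** There are two gaps between the stated question and the stated method.

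First, baseline is a covariate and not a repeated level. For outcomes rated only before and after treatment, the repeated levels are therefore the two post-treatment ratings. The tests that such a model prints by default are a group effect averaged over the two visits and a group-by-time interaction. Neither is the arm difference at 2 weeks or at 6 months. The interaction asks only whether the arm difference changes between visits, so a fully sustained benefit makes it null. It would bear on efficacy if baseline were a repeated level, which makes it easy to misread here.

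Second, a classical repeated-measures general linear model keeps only people with a complete set of ratings. Without imputation, the 2-week comparison would then be limited to those who also answered at 6 months. That loses precision and selects on later response. The section describes no other analysis that does without LMCF, so the loss falls on the one available check of that imputation.

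**Working it through.** **1. The plan's own figure.** Sample size section: differences of 7 points (SD 12) and 4 points (SD 7), effect size 0.57, two-sided alpha 0.05, power 0.80, about 50 per group. A two-sample t-test with the noncentral t distribution at d = 0.57 gives 50 per group (power 0.806). The figure reproduces. It is sized for one between-arm difference, not for a visit average or an interaction.

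**2. Can the model give the stated differences?** Yes. Let M be the adjusted arm effect on the mean of the two visits, and D the adjusted arm effect on the first visit minus the second. Then:

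- 2-week difference = M + D/2
- 6-month difference = M − D/2

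In a simulated complete data set (79 per arm), M + D/2 was −0.5087, equal to the ANCOVA at the first visit. M − D/2 was −0.1277, equal to the ANCOVA at 6 months. The estimates are in the model and have to be requested.

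**3. Does it matter which result is read?** Assumptions: 159/2 = 79.5 per arm, unit residual SD at each visit, d1 = 0.57 at 2 weeks, between-visit correlation r of 0.4, 0.6 or 0.8. The correlation and the 6-month effect d2 are not in the document.

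- Standardised averaged effect = ((d1 + d2)/2) / √((1 + r)/2)
- Standardised interaction effect = (d1 − d2) / √(2(1 − r))

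| 6-month effect d2 | Power, 2-week contrast | Power, averaged test (r = 0.4 / 0.6 / 0.8) |
|---|---|---|
| 0.57 (sustained) | 95% | 99% / 98% / 96% |
| 0.20 | 95% | 82% / 77% / 72% |
| 0 | 95% | 57% / 51% / 47% |

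With d2 = 0.57 the interaction effect is zero, so its test rejects 5% of the time although both per-visit effects are real. The averaged test gains power if the effect is sustained and loses power if it fades. The results answer different questions, so the plan should say which is the efficacy result.

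**4. Loss in the analysis without LMCF.** Let p1 and p2 be the proportions of that population rated at 2 weeks and at 6 months. No more than min(p1, p2) can be rated at both. With p2 < p1:

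- Share of 2-week ratings discarded ≥ 1 − p2/p1
- Ratio of standard errors ≥ √(p1/p2), with similar loss in both arms

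The document gives neither rate. Under assumed values:

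| p1 | p2 | 2-week ratings discarded, at least | Standard error larger by at least |
|---|---|---|---|
| 0.90 | 0.80 | 11% | 6% |
| 0.90 | 0.70 | 22% | 13% |
| 0.90 | 0.60 | 33% | 22% |
| 0.80 | 0.70 | 12.5% | 7% |

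These are minima, reached when everyone who answers at 6 months also answered at 2 weeks. If missingness at the two visits is independent, the share discarded is 1 − p2, which is 30% at p2 = 0.70.

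**The case against.** A reader might infer that the plan has adopted the averaged effect or the interaction as its test, or that the model cannot answer the question. The document supports neither. It mentions neither term, it states the aim as differences at the two times, and step 2 shows that the same model yields both differences exactly. It is also a condensed article, and naming a contrast is commonly left to a full analysis plan. That stands: taken alone, the first half is an unnamed contrast and would not justify replacing the model. The power losses for a fading effect must also be set beside the gain under a sustained one.

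The two-level structure is an inference too. IAS and the global quality of life scale are rated after every session, and the ASRS-A and CSDS have a self-rating half-way through the skills training. For those outcomes the repeated levels are less certain.

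On missing data, the main analysis imputes, so the loss is confined to a sensitivity analysis already limited to treatment completers. Its size rests on assumed response rates, and a mixed-model fit would avoid it. All true. But the section says general linear models, attending sessions does not guarantee a rating six months later, and this analysis is the stated check on LMCF.

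**Conclusion.** The point holds in limited form. The article fixes a model without tying it to the two per-visit arm differences it sets out to estimate, and the model's default group tests are not those differences. This is a gap in specification, not a model that is unable to answer.

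The more concrete defect is in the completer analysis without LMCF. If the general linear model is fitted in its classical form, that analysis keeps only participants rated at both visits and discards observed 2-week ratings. The main analysis is unaffected. The loss cannot be derived from the document. At assumed response rates of 90% and 70% it is at least 22% of 2-week ratings, with a standard error at least 13% larger. Other plausible rates move these figures as shown in the working.

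**What to change.** Fit a likelihood-based mixed model for repeated measures with arm, visit, arm-by-visit, baseline, baseline-by-visit and an unstructured within-person covariance. Use it at minimum for the analysis without LMCF, and include every participant in that analysis's population who has at least one post-treatment rating. Report the arm difference at 2 weeks and at 6 months, each with a 95% CI, as the efficacy results. State that group-by-time describes persistence only.

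There is one small downside: participants with no post-treatment rating contribute nothing to this model. Report their number by arm, and keep the baseline-completer set (159 adolescents, 162 parents) as the reference population.

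The cost is analysis-plan wording before the analysis starts in summer 2019. The data are the same, the software is standard, and no extra participants or visits are needed.
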